The three domains of recovery (clinical, functional and personal) complement each other but do not necessarily develop simultaneously during the recovery process [18–21]. Being in symptomatic or clinical remission does not inherently mean that someone has found a new balance in life in which they can cope with the difficulties resulting from the illness. Functional and personal recovery can lag behind clinical recovery by up to several years [22–24]. One reason for this is a stronger feeling of incompetence caused by identifying oneself with the mental illness (illness identity), which has an impact on hope and self-esteem and in turn can negatively influence coping with daily tasks, social interaction and vocational outcomes [25]. Lasting effects in the functional and personal domains are known risk factors for symptomatic relapse [15, 26]. Consequently, interventions aimed at enhancing personal and functional recovery may also contribute to perpetuating clinical recovery and preventing relapse into new depressive episodes.

The above shows that we should ideally pay more attention to personal and functional recovery in depression treatment to optimise treatment outcome in MDD patients. However, current treatment guidelines are predominantly based on efficacy studies in which outcome is defined as clinical recovery [11, 27]. One barrier to adopting a broader approach to recovery in depression treatment may be that comprehensive and well-documented programs focused on functional and personal recovery in MDD patients are currently lacking. Recovery-oriented treatments have their origin in the field of schizophrenia treatment, where complete symptomatic recovery is rare due to the chronic nature of mental problems. Therefore, to enable patients to live with their symptoms and reach or maintain an acceptable quality of life, treatment is often focused on patients’ identity and on helping patients optimize their situation in other domains (e.g., social relations, work) [28]. To the best of our knowledge, such an approach has not yet been adopted in depression treatment. As many patients suffering from MDD also experience residual symptoms after remission [29] and a long-lasting impact of the illness on their identity and daily and social functioning (e.g., managing tasks at work/school and engaging in meaningful relationships) [30], recovery-oriented treatment could also be valuable for them. This type of treatment is the focus of this study.

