### Recruitment and randomization

Participants are recruited from October 2022 to June 2024 from several mental healthcare organizations in the North of the Netherlands (including the University Center of Psychiatry [UCP] from the University Medical Center Groningen [UMCG], Mental Health Services Drenthe [GGZ-Drenthe], and Dimence).

Patients can be included in the study if they are between 18 and 65 years old, receive treatment for MDD and have depressive symptom severity levels that have decreased to moderate or less, according to the Inventory of Depressive Symptomatology self-report (IDS-SR). Exclusion criteria are: a primary diagnosis of bipolar depression or depression with psychotic features, comorbid schizophrenia spectrum or other psychotic disorder, comorbid moderate or severe dependence on alcohol or drugs, and neurological disorders (e.g., dementia). Additionally, patients with insufficient command of the Dutch language, cognitive problems or indication of low IQ (i.e., < 80), who do not possess a computer or smartphone, and/or who have been referred to a different mental health service for other mental problems are excluded.

In the participating centres, treating clinicians will inform eligible patients about the study and provide contact information to the coordinating researcher (DW) when a patient is willing to participate. Also, information about this study will be shared on different social media platforms, allowing interested participants to contact the coordinating researcher themselves. Once a patient has expressed their interest in participating, a researcher will contact them to further explain the study and check eligibility. An information letter will be sent, and a patient will have a week to contemplate, after which they will be contacted again. When a patient is willing to participate, a meeting will be planned with a researcher to discuss any further questions and to sign an informed consent form.

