After informed consent is obtained, patients will be randomly allocated to one of the study arms. Randomization will be performed at the patient level by a research assistant who is not involved in the study, using simple randomization with a 1:1 allocation ratio. A list with 140 randomly generated numbers (0 or 1) will be used to allocate patients in order of the date and time of the informed consent meeting. Patients who are randomized to the active intervention condition will be placed on a waiting list for the treatment in (a) the organization where they received all their previous treatment (for patients referred from organizations that offer the STAIRS training) or (b) in the UCP (for patients who are referred from organizations that do not offer the STAIRS training). The STAIRS training starts when at least three patients have been added to the waiting list. At that time, patients will receive an email inviting them to join the training. This email will contain all needed information about the date and location of the meetings and how to access the private online environment that is used as part of the STAIRS-program. When attending physical meetings turns out to be difficult for participants in the intervention condition, they will be given the option to follow the STAIRS training online. Previous pilot work showed this to be a usable and acceptable option [45].

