### Statistical analysis

#### Power calculation

Based on previously conducted meta-analyses on the effect of psychosocial interventions [71], behavioural activation treatment [72] and supported internet-based treatment [73] on the social functioning of patients with depression, a medium effect size is expected. The sample size estimation for the RCT was based on a Cohen’s d of 0.5, a *p*-value cut-off (alpha) of 0.05 (Z_alpha_ 1.96) and a power (1-beta) of 80% (Z_beta_ 0.84). The following calculation was used to obtain the number of needed participants per group (n_gr_): N_gr_ = (SD_gr1_ + SD_gr2_/ratio) * ((Z_alpha_ + Z_beta_)/d)^2^, where the ratio between the two groups’ sample sizes (n_gr1_/n_gr2_) was set to 1 (equal group sizes). This calculation resulted in (1 + 1/1) * ((1.96 + 0.84)/0.5)^2^ = 2 * 31.4 = 62.8) an estimated 63 participants needed per group (total sample size = 126). With an expected dropout rate of 10%, we arrived at a total required sample size of 140 ((126/9)*10), with 70 participants per treatment group.

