### Data analysis

#### Quantitative analyses

Before the start of the analyses, any missing values will be imputed 20 times using a fully conditional specification [74]. After multiple imputation, all analyses will be conducted in each of the 20 datasets and pooled across imputed datasets [75]. No subjects will be excluded in any phase of the data preprocessing and analyses. All analyses will be conducted according to the intention-to-treat (ITT) principle, and findings will be reported following the Consolidation of the Standards of Reporting Trials (CONSORT) guidelines [76].

The primary outcome in this study is the change in the level of subjective experienced recovery during the intervention period (T0 to T1) and at the six-month follow-up (T0 to T2). The efficacy of the STAIRS-training will be examined by comparing the change in recovery scores between the intervention group and the control group using linear regression models with the treatment group (0 = control; 1 = intervention) as the main independent variable. In subsequent analyses, subgroup differences in the change in the primary outcome will be explored by testing the interaction effects of treatment condition with a range of baseline covariates: age, gender, marital status, employment status, level of education, family composition, number of previous depressive episodes, duration of current depression, first age of onset, and sleeping problems. Intervention effects on the continuous secondary outcomes are analysed using the same approach as for the primary outcome. To investigate the effect of treatment on the relapse rate (during follow-up; T1 to T2), logistic regression will be used with relapse at T2 (1 = yes; 0 = no) as the outcome and the treatment group as the independent variable.

For all estimated linear regression models, assumptions of conditional normality, linearity and homoscedasticity will be checked by inspection of Q‒Q plots and residual plots. In case of assumption violations, outcome variables will be transformed (e.g., natural logarithm) and models rerun. If necessary, different transformations will be applied until the model assumptions are met. Imputation and statistical analyses will be conducted with SPSS and/or R. A two-sided alpha level of 0.05 will be used.

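### The relapse model contains treatment group only, so it forgoes a modest, nearly free gain in precision from baseline risk information

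*Protocol article*

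**What the plan says.** The relapse sentence in the protocol article, Quantitative analyses, reads "logistic regression will be used with relapse at T2 (1 = yes; 0 = no) as the outcome and the treatment group as the independent variable". For the continuous outcomes the same section describes "using linear regression models with the treatment group (0 = control; 1 = intervention) as the main independent variable". The word *main* there leaves room for further terms; the relapse sentence has no such word.

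No other section adds a covariate for relapse. Baseline covariates, including number of previous depressive episodes, appear under Quantitative analyses only for interaction tests on the primary outcome. Sample characteristics mentions baseline data only for studying how patient characteristics alter the effect of STAIRS. The between-group methods mentioned in the Discussion deal with delivery in groups.

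Under Recruitment and randomization, patients are allocated "using simple randomization with a 1:1 allocation ratio", directly after consent. To enter, they must "have depressive symptom severity levels that have decreased to moderate or less, according to the Inventory of Depressive Symptomatology self-report (IDS-SR").

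**The concern.** The continuous outcomes are analysed as change from T0, so each patient's starting level enters the comparison. Relapse has no change score, and neither the model nor the design takes starting risk into account. If baseline severity or episode history predicts relapse, leaving it out lowers power somewhat, and any chance difference between arms passes into the odds ratio.

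Relapse belongs to the first of the secondary hypotheses in the Background, and the Discussion says that a lower relapse probability would add weight to the case for recovery-oriented programs. The trial was sized for a continuous outcome only, so a yes/no outcome has little information to spare. Naming covariates in advance also removes the temptation to adjust after an imbalance has been seen.

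**Working it through.** **Inputs from the protocol article.** d = 0.5, 80% power and 10% dropout (Power calculation); two-sided alpha 0.05 (Quantitative analyses); simple 1:1 allocation. **Assumptions, because the protocol gives no figures.** Control relapse 20%, 30% or 40%; marginal odds ratio 0.50 or 0.35; two independent standardised baseline predictors, each with an odds ratio per SD of 1.25 (weak), 1.5 (moderate) or 2.0 (strong).

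**1. The plan's own figure.** 2 × ((1.96 + 0.84)/0.5)² = 62.7, so 63 per arm and 126 in total; 126/0.9 = 140. This reproduces, but it covers only the continuous primary outcome. No power is stated for relapse.

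**2. Unadjusted power for relapse, 63 per arm, odds ratio 0.50.** The STAIRS rate p1 follows from odds p1/(1−p1) = 0.5 × p0/(1−p0). Power = Φ{(|p0−p1| − 1.96√[2p̄(1−p̄)/n]) / √[(p0(1−p0)+p1(1−p1))/n]}.

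For p0 = 0.30: p1 = 0.176 and p̄ = 0.238, so (0.1235 − 1.96 × 0.0759)/0.0751 = −0.335, and power is 36.8%. For 20% against 11.1% it is 27.8%; for 40% against 25% it is 43.5%.

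The plan imputes missing values and excludes no one, so 140 patients are analysed. With 70 fully observed patients per arm the figures would be 30.4%, 40.2% and 47.4%.

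**3. Gain from adjustment.** 4,000 simulated trials per scenario, N = 126, two-sided Wald test. Power with treatment only → with both covariates:

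| Control relapse | Marginal OR | Weak (1.25) | Moderate (1.5) | Strong (2.0) |
|---|---|---|---|---|
| 20% | 0.50 | 26.7 → 27.4% | 26.2 → 27.4% | 26.1 → 28.4% |
| 30% | 0.50 | 35.1 → 36.5% | 35.3 → 36.7% | 35.1 → 40.5% |
| 40% | 0.50 | 43.3 → 43.8% | 43.5 → 46.0% | 43.1 → 48.8% |
| 20% | 0.35 | 47.0 → 47.3% | 46.1 → 47.7% | 46.2 → 50.3% |
| 30% | 0.35 | 63.2 → 63.6% | 63.7 → 65.2% | 63.3 → 69.3% |
| 40% | 0.35 | 73.7 → 74.2% | 74.1 → 76.9% | 73.8 → 79.9% |

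The gain is 0.3 to 2.8 points for weak to moderate predictors and 2.3 to 6.1 points for strong ones. With no treatment effect, the type I error was 4.5–5.7% unadjusted and 4.4–5.9% adjusted.

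**4. Chance imbalance.** The standardised baseline difference between arms has SE 2/√126 = 0.178. For two predictors the imbalance on the log-odds scale has SD √2 × ln(OR) × 0.178, which is about 0.06, 0.10 and 0.17 for ORs of 1.25, 1.5 and 2.0. A 2-SD imbalance with strong predictors shifts the odds ratio by a factor of about exp(2 × 0.175) = 1.4.

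For scale, at 30% against 15% and 63 per arm, SE(log OR) = √(1/18.9 + 1/44.1 + 1/9.45 + 1/53.55) = 0.447. One covariate with slope 0.8 per SD contributes 0.8 × 0.178 = 0.142, or 0.142²/0.447² ≈ 10% of that variance.

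**The case against.** The strongest reply is that nothing here is incorrect. An unadjusted logistic regression in a randomised trial is a valid analysis, and covariates for secondary models are often settled in the SAP. The first half stands: a reader might infer that the odds ratio is biased or the test unsound, but the type I error is held and chance imbalance averages out over randomisations. The ordinary confidence interval already allows for it. The second half stands only in part, because the sentence does not leave the model open; it names treatment group as the independent variable.

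A reader might also infer a large power gain. With one covariate, 30% against 15% relapse and 126 patients, simulated power rises from 51% to 62% at a log-odds slope of 1.6 per SD, which is an odds ratio of exp(1.6) ≈ 5. At a slope of 1.2 (odds ratio about 3.3) it rises from 53% to 61%. Nothing in the protocol supports predictors that strong, and the severity ceiling at entry restricts the range of the IDS-SR, which tends to weaken it.

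Nor does the protocol itself name these covariates as predictors of relapse. The Background says "Lasting effects in the functional and personal domains are known risk factors for symptomatic relapse", which concerns functional and personal effects rather than the IDS-SR or episode history. It shows only that the protocol accepts that relapse risk differs between patients.

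Finally, it is not established that the fix needs no new data. The IDS-SR is an eligibility threshold, but no section says that the score is kept in the trial dataset. The scheduled T0 IDS-SR comes in the week before the intervention, which in the STAIRS arm is after allocation and the waiting list. This objection stands and shapes the fix.

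**Conclusion.** The point holds as a modest matter of efficiency on a secondary outcome. Under the assumed relapse rates and predictor strengths, adjustment adds about 0 to 3 points of power for weak to moderate predictors and 2 to 6 for strong ones. It also removes the part of the chance imbalance that those predictors carry. It does not rescue the relapse comparison: at an odds ratio of 0.50, power is roughly 26–43% without the covariates and 27–49% with them, so the limit is the sample size. The change is worth making because it costs almost nothing and the covariates would be fixed before the data are seen.

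**What to change.** Under Quantitative analyses, replace the relapse model with a logistic regression of relapse (T1 to T2) on treatment group, number of previous depressive episodes and the IDS-SR score from the eligibility check. State whether that score is recorded in the trial dataset. If it is not, adjust for number of previous episodes in the main analysis and add the T0 IDS-SR only as a sensitivity analysis, because T0 follows allocation. Episode history is little affected by allocation even if it is recorded at T0.

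Report the standardised (marginal) risk difference and odds ratio from the adjusted model, with the unadjusted model as a sensitivity analysis.

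The cost is one sentence and up to two degrees of freedom. At an odds ratio of 0.50 the assumed rates imply about 20 relapses (63 × 0.20 + 63 × 0.111) to 41 (63 × 0.40 + 63 × 0.25), so two covariates are manageable, though tight at the lower end. The conditional odds ratio differs from the crude one (with strong predictors about 0.45 where the marginal value is 0.50, at 30% control relapse); the standardised estimate deals with this.

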#### Qualitative analyses

Qualitative analyses will be performed according to the Qualitative Analysis Guide of Leuven (QUAGOL) [77]. The analysis process described in the QUAGOL consists of ten stages, in which the data are thoroughly read and reread to reach meaningful concepts, come to a conceptual framework and use the findings to answer the research question. All semi-structured interviews will be audio recorded and transcribed verbatim immediately by the interviewing researcher (DW), and a short report about each patient’s characteristics and the context of the interview will be written in the first stage. This transcript will be read different times by DW and another member of the research team to become familiar with the data. The researchers’ first interpretations of passages and key phrases will be written down. In the second stage, a brief summary will be written of each interview containing the key storyline as a narrative report. For the first five interviews, this will be done independently by two researchers, after which the narrative report will be discussed with another member of the research team. A member check will be done by sending the report to the patient who has been interviewed and asking if they recognize themselves in what has been described [78]. Stage three consists of the development of a conceptual interview scheme in which the patients’ experiences will be replaced by more abstract concepts. This means that important data will be filtered from the interview and clustered into concepts. Next, in stage four, the conceptual interview scheme of each interview will be compared with the interview on which it is based to check if it reflects the most important concepts. If needed, the interview scheme will be adapted, completed or refined. In stage five, the concepts will be compared across interview schemes to identify a list of common concepts. New concepts can be added to this list if needed, and comparable concepts can be merged into one, where appropriate. In stage six, the coding process starts. Here, the concept list will be evaluated and discussed by the research team. The resulting list of concepts will then be transferred as codes to Atlas.ti. In stage seven, all interviews will be read thoroughly again, and significant passages are given a code. Questions regarding the concepts and/or possible necessary changes to the list are noted and discussed in the research team, after which the list may be adapted. After coding, one-third of the interviews will be analysed independently by two researchers in stage eight to check if all citations indeed match the code and to specify the different concepts by adding the context (when, why, under which circumstances, etc., do the concepts appear). In stage nine, all concepts are integrated into a conceptual framework, which will be used in stage ten to systematically describe the findings with regard to the experienced effects, the mechanisms contributing to it and the usability and acceptability of the STAIRS program. These findings will be discussed by the research team to answer the research question.

### Economic evaluation

As part of the RCT, the cost-effectiveness of STAIRS will be evaluated. Analyses will be performed using the societal perspective, as we are interested in all relevant costs, including direct costs (healthcare costs) and indirect costs (productivity loss). Healthcare costs will be calculated by multiplying the healthcare resource use (general practitioner visits, hospital days, etc.) during the last three months, as assessed with the TIC-P, by their reference cost prices as described in the guideline for economic evaluation [79]. The costs for delivering the intervention will be calculated by multiplying the number of hours spent by both trainers per group by the average hourly wage of a clinician and an expert by experience according to the collective employment agreement for Dutch mental healthcare and dividing this by the average number of participants per group. Productivity loss will be calculated by summing the costs of absenteeism and presenteeism. Absenteeism will be calculated using the friction cost method by multiplying the lost working hours in the last month by an average hourly wage. The percentage of work loss due to presenteeism will be calculated by multiplying the percentage of lost productivity while at work (indicated by patients on a 0–10 range) by the number of hours affected. Although productivity loss is expected to be less important in the studied population, as unemployment is relatively high, data on productivity loss will be collected anyway because the intervention under study is also targeted at regaining satisfactory functioning in a (paid or unpaid) job again. All reference cost prices and average hourly wages will be corrected based on inflation rates to represent realistic costs for the present time.

The cost-effectiveness of CAU + STAIRS versus CAU + basic psychoeducation will be analysed by calculating the incremental cost-effectiveness ratio (ICER). For this, the difference in total costs of both interventions (healthcare and productivity costs between T0 and T1/T2, plus the costs of deploying the intervention) will be divided by the difference in effect of both interventions. The incremental costs will be reported per QALY gained as well as per point gained on the I.ROC to provide insights into both the cost-utility and the cost-effectiveness of the STAIRS program.

We expect a significant difference between participants in both interventions in the level of recovering quality of life and consequently in QALYs, favouring the STAIRS-program. Furthermore, a reduction in healthcare and productivity costs is expected for the STAIRS group. As the costs for delivering the STAIRS-training are low, the ICER is expected to be well below the threshold set by the National Health Care Institute, showing that STAIRS is a cost-effective program. If there is no significant difference in the level of recovering quality of life between STAIRS and the control group at the 6-month follow-up (T1), but a positive trend is visible, we will model a future expectation with a best case, conservative case and worst case scenario. Based on these scenarios, the possible long-term cost-effectiveness will be calculated.

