### Interventions

All patients who are included in the RCT will continue to receive CAU according to applicable clinical guidelines during the complete runtime of the study. CAU can consist of psychotherapeutic and/or drug treatment, outpatient, day or inpatient treatment and individual or group treatment.

The main goal of the STAIRS program is to increase the level of functional and personal recovery of patients suffering from the lasting impact of depression on their lives. This will be done with different exercises, by sharing experiences and by providing supportive information. The STAIRS training has a duration of eight weeks, in which participants address the following themes in weekly group sessions: effects of depression and treatment, structure, public stigma and self-stigma, self-image, meaningfulness, connecting to others, relaxation and preventing relapse. Each session will be guided by a clinician (psychologist, nurse practitioner or medical social worker) and a certified expert by experience. Trainers will undergo a 1-day train-the-trainer where the aim of the program and the working methods used are discussed, the complete program is reviewed and example exercises are practised. In between sessions, participants can keep working on a theme via homework assignments on which they will be asked to reflect and interact with each other in a private online community.

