This study also has some expected difficulties. First, recruitment may be difficult because of the timing of the interventions in this trial. Patients are recruited during the final phase of their treatment and may therefore be reluctant to participate, as this may feel as a delay of the completion of their treatment. To minimize this risk, we emphasize to patients that STAIRS is an add-on to regular treatment with a specific focus on areas that are considered important by patients themselves in the final phase of treatment. Second, treating clinicians may be reluctant to inform eligible patients about the study because they might have concerns about not being able to end regular treatment during the runtime of the trial. We will therefore emphasize to clinicians that nothing needs to be changed in the current treatment. If the treatment is scheduled for completion during the RCT, this will not change because of participation in this study. Third, because the STAIRS-training is a group intervention, patients assigned to the STAIRS-training have to wait before they can start until enough subsequent patients are randomized to the STAIRS condition to fill up a group. If recruitment is slow, a trade-off may be necessary between reducing the waiting time for patients on the one hand and achieving the target group size on the other. To prevent patients from having to wait too long, a group can start when at least three patients are assigned. However, group dynamics in smaller groups may differ from those in larger groups, which may lead to different results. We will therefore compare the results of different groups based on group size to investigate possible differences. As the group sizes of existing group training programs within mental health care also differ, insight into possible differences can also be helpful when implementing the STAIRS program in daily practice. Last, some patients may be reluctant to join face-to-face group meetings because they feel too exposed or have practical objections, such as excessive travel time. To give these patients the opportunity to participate, the STAIRS program can also be offered online. However, efficacy, patient experiences and cost-effectiveness may differ between the face-to-face and online version of the program. When analysing the data, we will use methods that can account for possible differences between groups, while taking into account a control condition that is ungrouped [81]. Furthermore, the results from the semi-structured interviews will be compared between patients who followed the STAIRS program face-to-face and those who followed the program online. Finally, in addition to overall cost-effectiveness, the cost-effectiveness per program version will also be assessed and compared.

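### STAIRS delivery is costed on trainer hours alone under a societal-perspective label, so venue, online environment, patient travel and possibly trainer training are left out

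*Protocol article*

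**What the plan says.** The Economic evaluation section of the protocol article sets the perspective: "Analyses will be performed using the societal perspective, as we are interested in all relevant costs". It names healthcare costs and productivity loss as the two classes. Healthcare use from the TiC-P is multiplied "by their reference cost prices as described in the guideline for economic evaluation".

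The cost of delivering STAIRS has its own rule: "multiplying the number of hours spent by both trainers per group by the average hourly wage" for the two trainer roles, and then "dividing this by the average number of participants per group". No other delivery item is named. The ICER numerator is the between-arm difference in healthcare, productivity and intervention costs.

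Other sections describe further resources that STAIRS uses:

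- Interventions: "Trainers will undergo a 1-day train-the-trainer". There are eight weekly group sessions and a private online community.
- Recruitment and randomization: meetings have a location. Patients referred from organizations that do not offer STAIRS are placed at the university centre. Access to the private online environment is part of the invitation.
- Discussion: some patients may be reluctant to meet face to face because they feel too exposed "or have practical objections, such as excessive travel time", and this is a reason for offering an online version. The same paragraph commits to comparing cost-effectiveness between the two versions.

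**The concern.** The stated perspective is wider than the stated costing rule. The omitted items are non-negative and fall on the STAIRS arm, so a delivery cost computed by the rule can only be too low or, at best, right. The section goes on to expect an ICER well below the national threshold because delivery costs are low, so the costing rule supports the premise of that expectation.

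The comparison between versions has a further weakness. Travel is one of the document's own reasons for going online, yet neither travel nor venue can enter the cost of either version.

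**Working it through.** The article states no delivery cost, so there is no figure to reproduce. The check compares the rule with the described resources and then shows what the omissions could amount to under assumptions.

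**Coverage**

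| Resource described | In the delivery formula? | In the TiC-P as described? |
|---|---|---|
| Trainer hours per group | Yes | Possibly again, if patients report sessions as provider contacts |
| One-day trainer training | Only if trainer hours include it | No |
| Private online environment | No | No |
| Venue (face-to-face) | No | No |
| Patient travel | No | No |
| Patient session time | No | Partly, if it appears as lost work |
| Control letters | No | No |

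The TiC-P column rests on the Cost-effectiveness part of the measurement section: provider contacts in the first part, and loss of paid and unpaid work and reduced efficiency in the second.

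**Trainer training, in hours**

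From the document: 8 sessions, 2 trainers, 1 training day each. Assumed: session length h, an 8-hour day, and k groups per trainer pair.

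- Delivery hours per group = 8 × h × 2. With h = 2 this is 32.
- Training hours per group = 2 × 8 / k = 16 / k.
- Added share for h = 2: 16/32 = 50% (k = 1), 25% (k = 2), 10% (k = 5), 5% (k = 10).
- For h from 1.5 to 2.5 hours and k from 1 to 10, the share runs from 4% to 67%.

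**All omitted items, in illustrative euros**

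Every unit value here is an assumption: summed hourly wages W of 43 to 65, group size g of 3 (the document's minimum) to 10, venue V of 0 to 50 per session, platform 5 to 25 per participant, travel T of 5 to 25 per session, and training at 10% to 50% of trainer cost (k = 5 to k = 1).

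- Stated formula with 2-hour sessions: 8 × 2 × W / g. Lowest 16 × 43 / 10 = 68.8; highest 16 × 65 / 3 = 346.7 per participant.
- Smallest relative addition, face-to-face: (34.7 + 5 + 8 × 5) / 346.7 = 23%. Online: (34.7 + 5) / 346.7 = 11%.
- Largest relative addition, face-to-face: (34.4 + 25 + 8 × 50/10 + 8 × 25) / 68.8 = 299.4 / 68.8 = 435%. Online: (34.4 + 25) / 68.8 = 86%.
- If trainer hours already include the training day, these become 13% to 385% face-to-face and 1% to 36% online.

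**Between versions**

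With equal trainer hours and group size, the stated formula gives a difference of 0. With venue and travel, face-to-face minus online is 8V/g + 8T. This is 0 + 40 = 40 at the low end and 8 × 50/3 + 8 × 25 = 333 at the high end.

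**Effect on the ICER**

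An omitted net cost x moves the ICER by x divided by the difference in effect. The document gives neither, nor total costs per arm, so the shift cannot be computed.

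**The case against.** The strongest reply has four parts.

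- **The article is a condensation.** Itemised unit costs may be in a fuller document, and the costing sentence never says that nothing else will be counted. The same sentence that claims a societal perspective also spells out healthcare and productivity costs, so the mismatch is partly one of wording. This reduces the weight of the point but does not remove it. The article does not leave the delivery cost open; it gives a rule, and applying that rule as written omits resources that the article itself describes.
- **The net direction is less certain than it looks.** The control letters are also uncosted, which works the other way, though the Interventions section calls the added elements minimal. Sessions are led by a clinician, and the three-month TiC-P window at T1 covers an eight-week programme that has just ended. Patients may therefore report sessions as provider contacts, which would partly count delivery twice, against STAIRS. This stands, and the fix has to deal with it.
- **Patient time may already be counted in part.** Sessions in working hours can appear as absenteeism. This also stands. A reader might infer that all patient hours must be added, but that risks double counting, and whether to value remaining leisure time is a debatable choice.
- **The version comparison still has content.** Trainer hours, mean group size, TiC-P costs and effects can all differ. A reader might infer that the comparison is empty or should be dropped. The documents do not support that: nothing states that trainer hours are equal across versions, and only the venue and travel differences are shut out.

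**Conclusion.** The point holds in a limited form. The delivery-cost rule is narrower than the perspective it serves, and it understates STAIRS delivery cost by an amount that the document does not allow to be fixed. The percentages above are shares of delivery cost only and rest on assumed session length, groups per trainer pair, wages and unit prices.

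A reader might go further and conclude that the ICER is materially biased, or that a finding of cost-effectiveness would be overturned. Nothing in the document shows this: the amounts per participant may be modest against total healthcare and productivity costs, and the effect on the ICER is unknown. The primary efficacy analysis is not affected. The correction is worth making because it is cheap and because the plan relies on delivery being low-cost.

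**What to change.** Revise the costing rule in the Economic evaluation section as follows:

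1. Add to the STAIRS cost, separately by version: trainer training spread over the groups run (or state that trainer hours already include it), the online platform, the venue for face-to-face groups, and patient travel.
2. Cost the control letters.
3. State how STAIRS sessions will be kept from also being counted as TiC-P provider contacts, and session time from also being counted as productivity loss.
4. If travel is not costed, describe the perspective as healthcare plus productivity, test the omitted items in a sensitivity analysis, and state that the comparison between versions does not reflect venue and travel differences.

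The cost is a little more costing work and a slightly less favourable ICER. The document does not say that travel or attendance per session is recorded, so simple, stated assumptions on travel will be needed. No change to design, sample size or patient questionnaires is required.
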